## Abstract

**Background:**

Extant research has long documented the association between domestic violence and homelessness. Yet, there appear to be few interventions to address the housing needs of survivors of domestic violence, and none on a digital platform.

**Objective:**

Our primary objective is to determine the feasibility of a full-scale intervention trial of a web-based tool that screens and educates survivors of domestic violence on affordable housing programs in New York City. Our secondary objectives are to assess the perceived usability and acceptability of the tool.

**Methods:**

The study will take place in a community-based domestic violence center in New York City. Treatment will consist of study participants not using (SC) or using (SC+) the tool, in or outside of private meetings with a case manager to discuss housing and other benefits. The frequency of the meetings will vary depending on the participant’s needs. The study will measure changes in housing knowledge, housing self-efficacy, and staff trust through two electronic surveys, administered at times 0 and 2 weeks. Following a historical cohort control group design, we will sequentially recruit participants, starting with SC and followed by SC+. After data collection for SC+ ends, we will invite staff from the partner site to individual, web-based interviews to share their experiences of and recommendations for implementing the tool.

**Results:**

Recruitment for the SC arm commenced in March 2022 and was completed in April 2023. After a year, 23 participants completed the study: 75 were screened, 44 were deemed eligible, 35 enrolled, and in the end, 23 participants completed baseline and follow-up surveys. Given the length of time it took to recruit for SC and the limited time overall that we had for the study, the study team decided to follow an expedited recruitment timeline for SC+. Recruitment for SC+ commenced in January 2024 and is anticipated to end by May 2024. Recruitment for the staff interviews will take place in June 2024. We expect to complete the study and be ready to compile the results by the end of June 2024.

**Conclusions:**

The protocol describes a feasibility study that can inform future research on housing or digital tools for a similar study population. Data from the study will also be used to inform revisions to the tool.

**International Registered Report Identifier (IRRID):**

DERR1-10.2196/63162

## Introduction

### Background

Survivors of domestic violence (survivors) in the United States are at heightened risk of homelessness [1,2]. Homelessness refers to a state in which an individual does not have a fixed place to stay or is living in a place unsuitable for human habitation [3]. In New York City, more than 2 in 5, or 41%, of families entering the City’s homeless shelter system, run by the Department of Homeless Services (DHS), have attributed their homelessness to domestic violence [4]. Short-term emergency shelters, specifically for domestic violence in New York City, offer survivors much critical aid; however, one study found that one-quarter of survivors exiting from emergency shelters moved directly into DHS shelters [5]. Presently, over 86,000 individuals are served by DHS shelters on a given day [6], up from prepandemic estimates that hovered closer to 60,000 [4]. Against a backdrop of about 600 domestic violence–related calls to the New York Police Department a day [7], the numbers, alone, underscore the significance of homelessness and domestic violence in New York City. The research team of this feasibility study thus purposively selected New York City as the study setting given its disproportionate need.

Remarkably, considering the sheer magnitude of domestic violence and its bidirectional relationship with homelessness in the United States and New York City, few housing solutions have been designed to specifically address the housing needs of survivors of domestic violence. The few solutions that follow, however, show promise.

### Temporary Housing

Two common forms of temporary housing are emergency shelters and transitional housing. Emergency shelters are a type of homeless shelter allocated for use by survivors of domestic violence. In New York City, emergency shelters provide survivors with a temporary place of stay, for 90 days initially, with a possible extension of up to 180 days [8]. Transitional housing in New York City, likewise, offers survivors a temporary place of stay, for up to 2 years in facility-based or scattered-site programs. In facility-based programs, survivors reside in the same building; whereas in scattered-site programs, survivors receive rental subsidies to live in apartment sites scattered throughout the community or in their current homes if the abuser has vacated the home [9].

While little research to the best of our knowledge exists on temporary housing’s housing outcomes, prior research in the United States does suggest that emergency shelters and transitional housing lead to positive safety outcomes for survivors [10,11]. According to Messing et al [10], female survivors who left their perpetrators for emergency shelter experienced significantly less abuse during the follow-up period of 8 months than female survivors who did not seek emergency shelter. Findings from another study indicated that a longer shelter stay led to a lower degree of repeat abuse in the initial 6 months following a survivor’s exit from the shelter [11]. Although these studies did not take place in New York City, we can infer from their findings that emergency shelters and transitional housing can contribute to promising safety outcomes for survivors in New York City.

### Permanent Supportive Housing

Permanent supportive housing (PSH) programs offer individuals and families a government-subsidized place of stay, for which tenants typically contribute one-third of their income to rent [12], along with a broad range of support services to help tenants with their clinical and nonclinical needs [13]. In the United States, PSH’s benefits have included reductions in emergency and hospital use and substance use, and fewer encounters with the criminal justice system [14]. While PSH programs are available to and accessed by survivors in New York City, many have not been designed specifically for the needs of survivors. Many PSH programs, for instance, do not include safety planning, a critical strategy for survivors leaving their abusers [9].

Housing First (HF) [15] is a type of PSH program that prioritizes rapid housing placement. The HF model hypothesizes that helping someone obtain stable housing first will facilitate their subsequent ability to address other concerns; hence, HF programs seek to connect tenants with permanent, independent housing first, prior to addressing other issues [15,16]. Based on HF’s successes with adults with mental illness and substance abuse issues, agencies across the United States are now exploring adaptations of HF for domestic violence. One such successful adaptation has been the Washington State Domestic Violence Housing First Program (DVHF) [16]. Designed with survivors’ needs in mind, the DVHF includes safety planning, as well as various support services, including home security and lock changes, counseling, career training, and legal services. Initial results have been promising. In the inaugural cohort of four agencies, the DVHF saw 89% of survivors retain, that is, maintain or obtain permanent housing by the end of the 18-month study period, as compared with one-third at the start of the study [17]; similarly, in the second cohort of nine agencies, the DVHF saw 88% of survivors retain housing by the end of the 36-month study period, as compared with about half at the start of the study [18]. In addition, DVHF in both studies led to increases in survivor-reported independence and positive shifts in needs and priorities [17,18].

Presently, there are no HF programs in New York City tailored for survivors of domestic violence. However, the promising performance of DVHF programs in states like Washington offers encouragement for their adoption in places like New York City.

### Rapid Rehousing and Flexible Funding

Besides DVHF, rapid rehousing and flexible funding are two other promising innovative models. Rapid rehousing refers to an approach consisting of an intensive housing placement effort including housing identification, a time-limited subsidy, and additional education and support to retain housing. Flexible funding refers to an approach in which domestic violence agencies may grant survivors discretionary funding for basic needs, like changing locks, moving, storage, or security deposits.

While research on these newer approaches has been sparse, a few published studies have supported their potential in helping survivors access and retain housing in the United States. In one study, 94% of survivors in an urban city who were about to lose housing at the start of the study reported positive housing outcomes just 6 months after receiving flexible funding [19]. A rapid rehousing pilot, moreover, found that, in comparison with participants given standard shelter services, rapid rehousing participants saw a reduction in the length of shelter stay and recidivism back to shelter [20]. While we are not aware of any peer-reviewed program evaluations in New York City, rapid rehousing and flexible funding both saw upticks in use among New York City–based domestic violence agencies during the COVID-19 pandemic [21,22].

### Gaps to Be Addressed

Currently, when a survivor asks their case manager, “What are my housing options?” and “What am I eligible for?” the case manager would typically collect information about the survivor, manually determine which options would work best and are available, explain the options to the survivor, and then apply for each option with the survivor. The process is arduous and could take a few months. In parallel, the survivor may receive different information from different sources, further complicating the process and leading the survivor to feel overwhelmed.

While the existing housing solutions, albeit sparse, have shown promise, there appears to be no digital solution that survivors can use to address their housing needs. This is especially salient given most adults (90%) in the United States, regardless of socioeconomic status, have smartphones, and more than half with browsing capability [23,24]. Digital solutions furthermore have served as promising complements to traditional services like counseling and advocacy [25-27]. Thus, there is an opportunity to develop a digital tool to address the housing needs of survivors.

### Description of the Tool

Knowing the above, the study team collaborated with a coalition of domestic violence housing specialists in New York City to create a web-based tool that both screens and educates survivors on affordable housing programs in New York City. Grounded in the process of empowerment [28], the digital tool strives to address survivors’ barriers to housing knowledge while building survivors’ self-efficacy to achieve their housing goals. Taking only a few minutes, the tool starts by collecting survivors’ household size, income, and living situation, and ends by generating curated matches of housing programs based on the survivors’ information (Figure 1). The tool gives the survivor the agency to determine and learn about their options, without the case manager serving as the sole gatekeeper of information. Because it is one tool, the survivor and case manager also reference the same information, thereby, standardizing the process and freeing up the case manager and survivor to focus on applying for housing programs.

It is important to note that the tool neither guarantees the survivor’s access to housing programs nor addresses every housing need of every survivor. Still, the tool introduces survivors to relevant, available housing programs, all from the convenience of their phones. The tool also serves survivors and nonsurvivors alike. Its content on housing programs is broadly relevant to anyone keen to determine their eligibility for affordable housing programs in New York City.

For this feasibility study, the study team will test the concept of the tool with a convenience sample of survivors served by a community-based domestic violence center (site) in New York City. The site serves a wide range of clients and is particularly attentive to the needs of survivors with disabilities.

**Figure 1 figure1:**
[figure not shown]
Snapshots of tool.

### This Study

This paper presents the protocol for testing the concept of the tool in a community-based domestic violence center. The feasibility study aims to determine whether implementing a web-based tool in this setting is possible; and whether the delivery of housing information through a digital tool could show promise of increasing survivors’ housing knowledge, housing self-efficacy, or trust in staff. In this paper, we use the terms “full-scale” or “large-scale” trials to denote next-phase trials that will be fully powered to measure impact. This study will compare the intervention with a control condition of no intervention use. We hypothesize that the intervention group will report greater increases in at least one of the primary outcomes: housing knowledge, housing self-efficacy, and staff trust, relative to the control condition. We also hypothesize that most survivors using the intervention will rate the tool as usable and acceptable.

### Research Questions

Through this study protocol, we are seeking to answer the following research questions: (1) What is the initial treatment effect of SC+ (standard care plus), as compared to SC (standard care), on survivors’ housing knowledge, housing self-efficacy, and staff trust? (2) What is the estimated sample size needed for a full-scale intervention trial? What is the estimated timeline needed to reach this sample size? (3) Are the expected rates of recruitment and retention achieved? (4) Are the study’s processes and instruments feasible for a full-scale intervention trial? and (5) Is the tool acceptable and usable by survivors and staff?

## Methods

### Study Design

The study will use a quasi-experimental, mixed methods design to assess the feasibility, usability, and acceptability of the tool (Multimedia Appendix 1). There will be two treatment groups: no use of the tool (standard care only, SC) and use of the tool (standard care plus, SC+). Survivors mostly come to the site through the organization’s crisis hotline. A survivor calls the hotline for help, and if deemed appropriate, the site makes an appointment for an intake interview to determine the survivor’s needs, including housing. Subsequently, a case manager is assigned to meet with the survivor. For new clients, the meetings normally take place twice a week during their first month. In these meetings, the case manager helps the survivor apply for a myriad of benefits, including housing programs if housing has been identified as a need. The meeting frequency then lessens as the survivor’s needs are met. SC will consist of no tool use, in or outside of the case manager meetings. SC+ will consist of tool use, in or outside of the case manager meetings. To ensure access to the tool regardless of whether a meeting is scheduled during the study period, the study team will email all SC+ participants a link to the tool for their self-use.

Following a historical cohort control group design, the study team will recruit participants into each arm, sequentially. We will recruit SC participants first. After all SC participants have completed their follow-up surveys, SC+ recruitment will begin. The SC and SC+ study groups will engage in two data collection points: one baseline survey prior to the housing meeting and one follow-up survey 2 weeks after completion of the baseline survey, each anticipated to take up to 30 minutes to complete. Study participants will be given a 1-week grace period to complete each survey. During SC+, the study team will email the tool to all enrolled participants following the completion of their first survey.

After SC+, we will engage five staff participants (key informants) in 60-minute individual interviews through a web conferencing platform like Zoom (Zoom Communications, Inc) about their experiences using the tool. The staff serve as decision-makers who can influence whether the tool will be used after the study. Thus, their perspectives are critical for understanding how to successfully implement the tool in the partner site and similar settings. Only 5 of the 12 staff met the eligibility criteria, which were determined in consultation with the partner site. We will not engage survivors in interviews to mitigate potential research fatigue [29]. We will, however, ask survivor participants about their experiences using the tool in the SC+ follow-up survey.

The study team had initially considered a randomized controlled trial (RCT) but selected a quasi-experimental, historical cohort design for several reasons. First, randomizing at the participant level, as in an RCT, was not feasible. Randomizing participants would have required the case managers to know the participant’s enrollment status and arm assignment to introduce the tool to the appropriate person. This lack of concealment could have produced differential treatment by the case managers based on the participant’s enrollment status. Second, we anticipated that tracking each participant’s arm assignment in an RCT would have added to the staff’s already limited capacities, a concern that the site also shared. Third and final, there was the concern that SC+ participants could interact with SC participants and share the tool, further confounding the results. Fortunately, the current historical cohort control group design mitigates the above risks. In the current design, case managers deliver SC, followed by SC+, regardless of whether a participant enrolls, thereby reducing any potential administrative burden on the staff. While the case managers are not entirely blinded to the participants’ enrollment status and arm assignment, the current design reduces the risk by emailing participants directly with the intervention link. If a participant mentions the link to the case manager, then the case manager will know that they have signed up for SC+. Otherwise, case managers will not know and will be encouraged to share the tool with all clients. Furthermore, the tool will only be accessible to participants during the SC+ arm, hence removing the possibility of participants interacting with the tool during the SC arm. To mitigate ethical concerns over one group and not the other receiving the tool, all SC participants will receive access to the tool after the SC+ arm completes data collection. Thus, while the study team had considered an RCT, the quasi-experimental, historical cohort control group design ultimately allowed the study team and partner site greater logistical flexibility, decreased administrative burden, and lower risk of confounding.

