### Study Population

The partner site, a community-based domestic violence program based in New York City, provides domestic violence and sexual assault counseling, case management, legal services, occupational therapy, and support groups for any survivor of domestic violence and is particularly attuned to the needs of survivors who are D/deaf or Hard of Hearing or have a disability [30]. Based on the last set of data collected by the site in 2021, the partner site, on average, served 171 new and existing clients per month. About 26% (n=45) of clients were new to the program each month. Of those who disclosed their information to the site, 84% (109/130) identified as a cisgender woman, and 15% (19/130) as a cisgender man. The majority identified as either Black (48/114, 42%) or Latino/a/x (32/114, 28%). None chose to disclose their employment status, but more than half (76/151) reported being on some form of public assistance. Finally, 52% (66/128) of clients reported a mental health disability, 18% (23/128) reported a sensory disability (ie, blindness or deafness), 17% (22/128) a physical disability, 10% (13/128) a medical condition, and 3% (4/128) a cognitive disability. The site has three full-time case managers, who cover a wide range of survivor needs including housing, and a full-time program director and assistant director who oversee the case managers.

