### Eligibility Criteria

Survivors, or participants, will be eligible for study inclusion if they consent to participate; are seeking assistance from the site at the time of joining the study; are at least 18 years old; have access to a device with web-browsing capability (eg, smartphone, tablet, or the site’s computers); are looking for housing; have a safe email account, with “safe” being interpreted as the survivor sees fit; can read English without assistance from others including translation or interpretation assistance; and have not participated in the study before. Staff, or key informants, will be eligible for inclusion in the study if they give oral consent to participate, are at least 18 years old, and bear the title or responsibilities of “case manager” or “director.” We expect to recruit five key informants.

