### Procedures

The two sequential study arms will follow the same procedures, differing only in treatment (Figure 2). In each arm, the program director will send a mass email about the study to their clients with the recruitment flyer and screening form link. The case managers may also refer prospective participants to the study in their individual meetings. If the prospective participant is interested, they will answer questions on a digital form to determine whether they meet the inclusion criteria. If the prospective participant meets all the inclusion criteria, the form will automatically collect their contact information, which will then trigger a digital consent form that will be emailed to the participant. If the prospective participant wishes to join the study after reading the consent form, they will click yes to proceed to the baseline survey. As we are waiving the collection of a signature to protect the participant’s confidentiality, clicking yes will constitute the participant’s consent to join the study. Should the participant proceed, they will receive the baseline survey immediately and a follow-up survey 2 weeks later, both by email. Each survey will be active for 1 week, and up to 3 email reminders will be sent to the participant during the 1-week grace period if the survey remains incomplete. If the participant completes the follow-up survey during the grace period, they will receive an additional email upon completion with the answer key to the knowledge quiz.

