**Figure 2 figure2:**
[figure not shown]
Participant flow. SC: standard care only; SC+: standard care plus.

During the 2-week period between the baseline and follow-up surveys, the participant will receive services as usual in the SC arm and services plus the tool in the SC+ arm. Regardless of whether a participant completes the surveys, the site will continue to provide services to the participant. In the SC+ arm, the study team will email the participant a link to the tool to use over the 2-week treatment period. The case manager will also share the tool in their individual meetings with SC+ participants. If there happens to be no meeting during a participant’s enrollment in the study, the participant can still access the tool through the study team’s email.

For each completed survey, the participant will receive a US $10 Visa eGift card via email for a potential total of US $20 for two completed surveys. Study data will be collected and managed using REDCap (Research Electronic Data Capture; Vanderbilt University) electronic data capture tools hosted at Johns Hopkins University [31,32]. REDCap is a secure, web-based software platform designed to support data capture for research studies, providing (1) an intuitive interface for validated data capture, (2) audit trails for tracking data manipulation and export procedures, (3) automated export procedures for seamless data downloads to common statistical packages, and (4) procedures for data integration and interoperability with external sources.

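### Baseline is said to precede the housing meeting, but enrollment is open at any stage of service, so service stage could confound the comparison of two-week change between the sequential arms

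*Protocol article*

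**What the plan says.** All references are to the protocol article.

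- **Timing of the surveys (Study Design).** Each arm has "one baseline survey prior to the housing meeting and one follow-up survey 2 weeks after completion of the baseline survey". The wording presumes one identifiable housing meeting that comes after baseline.
- **What standard care is (Study Design).** It is a series of meetings: "For new clients, the meetings normally take place twice a week during their first month". Intensity falls with time: "The meeting frequency then lessens as the survivor"'s needs are met.
- **Who may enter (Eligibility Criteria).** Among other conditions, participants "are seeking assistance from the site at the time of joining the study" and are looking for housing. No criterion concerns time with the site or earlier meetings.
- **How they are found (Procedures).** There are two routes: "the program director will send a mass email about the study to their clients with the recruitment flyer and screening form link", and "The case managers may also refer prospective participants to the study in their individual meetings". The baseline survey goes out immediately after the consent click.
- **Meetings in the window (Procedures, after Figure 2).** "If there happens to be no meeting during" a participant's enrollment, the emailed link still gives access to the tool.
- **Caseload (Study Population).** The site served 171 clients a month on average. "About 26% (n=45) of clients were new to the program each month".
- **Data and model (Sociodemographics; Statistical Analysis).** Length of time with the site is collected at baseline. Independent variables enter the difference-in-difference regressions only after prior tests of whether outcomes differ significantly by them.

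**The concern.** If baseline preceded standard care, the two-week change in SC would show what standard care does from its start, and the change in SC+ would show standard care plus the tool from the same point. Under the recruitment rules, some participants will answer the baseline survey after weeks or months of case management and others at the outset. The two weeks that follow then contain very different amounts of standard care.

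This matters for the comparison only if the mix of service stages differs between arms. The design leaves that open. SC was recruited from March 2022 to April 2023, and SC+ on an expedited timeline from January 2024 to an expected end by May 2024. Nothing restricts or balances service stage across the two periods. Difference-in-difference cancels a difference in starting level. It does not cancel a difference in expected two-week gain, which is what service stage could produce.

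The contrast has two uses. It decides the first Stop criterion (no positive change approaching significance in any primary outcome, relative to SC), and its effect sizes set the sample size of the full-scale trial. The Limitations section discusses incomplete blinding and setting, not service stage.

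**Working it through.** **1. The caseload figure reproduces.** 45/171 = 26.3%, the stated 26%. The remainder are existing clients: 171 − 45 = 126, and 126/171 = 73.7%. This describes all clients, not those eligible, so it shows that established clients are plentiful but does not estimate their share of enrollees.

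**2. The timing rule against the procedures.**

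| Study Design implies | What the other rules do |
|---|---|
| Baseline comes before the housing meeting | Consent triggers the survey; no meeting is involved |
| Standard care has not begun | No limit on time with the site or earlier meetings |
| A housing meeting follows baseline | Participants with no meeting in the window are provided for |
| Entry precedes case management | One recruitment route is a case manager meeting |

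**3. Standard care received in the window.** A first-month client: 2 meetings per week × 2 weeks = about 4. A later client: fewer, down to 0.

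**4. How this enters the estimate.** Let p be the proportion of an arm in its first month of service at enrollment, and g the mean two-week gain without the tool. Then

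bias in the difference-in-difference = (p in SC+ − p in SC) × (g first-month − g later).

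The documents give neither factor.

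- If enrollment in both periods mirrors the monthly caseload, p = 26% in each arm and the bias is (0.26 − 0.26) × anything = 0.
- Purely to show scale, assume a gap of up to 0.3 in either direction and a gain difference of 0.2 to 0.8 SD. The bias then lies between 0 and 0.3 × 0.8 = 0.24 SD, of either sign. A middle case is 0.2 × 0.5 = 0.10 SD.

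**5. Would the covariate rule catch a stage effect?** The rule tests whether outcomes differ by the covariate. Assume 23 completers per arm (the SC figure, taken for both), so 46 in all, and a two-sided 5% test by normal approximation.

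- Stage split as in the caseload: 0.26 × 46 ≈ 12 against 34. Standard error = √(1/12 + 1/34) = 0.336 SD. Power for a 0.5 SD stage effect = Φ(0.5/0.336 − 1.96) ≈ 32%.
- Most favorable split, 23 against 23: standard error = √(2/23) = 0.295 SD, and power = Φ(0.5/0.295 − 1.96) ≈ 40%.

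A stage effect of 0.5 SD would fail the preliminary test, and so be left out of the model, in about 60% to 68% of repetitions.

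**The case against.** Several points on the other side are sound.

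- **Baseline still serves the tested contrast.** The study team emails the tool after the first survey, and the comparison is SC+ against SC over the following two weeks. Earlier care does not spoil that. This stands, and it is why the point concerns the label on baseline and the comparability of the arms, not the validity of the survey.
- **Varying meeting intensity is disclosed.** It is standard care as delivered. This also stands, but disclosure does not make the mix equal across arms.
- **The housing meeting could mean the next one.** That helps only where there is a next one, and Procedures allows for none.
- **Referral in a meeting does not prove that a housing meeting has occurred.** Meetings cover many benefits. This stands: such a referral shows earlier case manager contact, not necessarily housing advice.
- **Length of time with the site is collected and may be tested into the model.** True, but the working shows how often a moderate effect would fail such a test.
- **This is a feasibility study,** and fully powered measurement of effect is left to a later trial. True, but its contrast still feeds a Stop criterion and a sample size.

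A reader might go further: add the site's 45 monthly arrivals to its existing clients over the two windows, conclude that the longer SC window holds a larger share of new clients, and infer a calculable bias against SC+. The documents do not support this. The sum counts as new anyone who arrived at any time during the window, including someone who enrolls a year later, when the relevant quantity is being in the first month at enrollment. Enrollment that follows the caseload gives no gap at all, and the mass email has no stated schedule. The bar on taking part twice removes some established clients from SC+, which works against the supposed direction. No passage says how much more early clients gain.

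**Conclusion.** The inconsistency is documented and needs correcting. Study Design describes a baseline before the housing meeting, while Eligibility Criteria and Procedures produce a baseline at enrollment, at any stage of service, followed by about four meetings to none.

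Confounding of the arm comparison by service stage is a possibility that the design leaves uncontrolled. It is not a demonstrated bias. No length of service by arm is reported, so size and direction are unknown and zero is a possible value. The 0 to 0.24 SD range rests wholly on assumed inputs. The conclusion that the covariate rule is a weak safeguard assumes about 46 completers and a stage effect near 0.5 SD.

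The point deserves action because the remedy is cheap and the contrast feeds the Stop decision and the planning of the full-scale trial.

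**What to change.** 1. **Reword Study Design.** State that baseline is taken at enrollment, before the study team emails the tool, whatever meetings have already taken place.
2. **Report service stage by arm.** Use length of time with the site, split into first month versus later, which is the cut that Study Design itself uses for meeting frequency.
3. **Prespecify it in the models.** Include this two-level variable in the difference-in-difference regressions for all three outcomes regardless of the preliminary significance tests. It must act on the change: as a covariate in a model of the two-week change, or as a stage-by-time term if both surveys are modeled as repeated measures. A main effect in a repeated-measures model would adjust the level only.
4. **Show the two-week change by arm within each stratum,** descriptively, beside the overall comparison.

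The cost is protocol wording, one table and, in a model of change, one degree of freedom. The variable is already planned for collection at baseline, and recruitment does not change. The strata will be small and their estimates imprecise, so they should be read as description and not tested.
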